### 13.3 Interim Analyses

1. There will be an interim analysis after completion of the 12 week visit for all 300 participants. This will include data from all Clinical Assessment Visits, but exclude data from phone visits out to 1 year and will be sufficient for early initiation of manuscript preparation.

### 13.4 Sample Size Calculation

**Outcomes:** The primary outcome for this study is biochemically confirmed 30-day continuous smoking abstinence at 12 weeks post TQD across all enrolled participants (intent-to-treat). Secondary outcomes include smoking abstinence at other time points (2 week visit), smoking reduction from baseline to follow-up visits, assessment of baseline variables as potential moderators of smoking behavior, assessment of psychological variables as potential mediators of smoking behavior, and assessment of economic outcomes. The sample size for this study was calculated based on effect sizes from prior studies on Varenicline and nicotine patch. Abstinence within these two arms will be assessed as secondary outcomes and are not expected to reach significance on all secondary outcomes. The study is powered to reach significance on the primary outcome (abstinence across the two arms combined).

**Nicotine Patch Based Treatment (secondary outcome):** Power calculation for Nicotine Patch Adaptive Treatment vs. Nicotine Patch Standard Treatment is based on abstinence rates observed in prior P50-funded trials. In one trial (Rose et al 2013), when participants received Nicotine Patch prior to their quit attempt, 41.2% showed >50% reduction in cigarettes-per-day (considered Patch Responders) whereas 58.8% did not show >50% reduction in cigarettes-per-day (were considered Patch Non-Responders). "Patch Responders" demonstrated biochemically-confirmed 4-week continuous abstinence at the 11-week post-quit attempt of 59.2%, whereas "Patch Non-Responders," when left on Nicotine Patch alone showed an abstinence rate of 16.0%. When however, the Patch Non-Responders were given Bupropion in addition to Nicotine Patch, they showed an increased abstinence of 28.3%. If our study were to show similar effect sizes as this prior study, the adaptive treatment group with 41.2% responders (abstinence rate = 59.2%), and 58.8% non-responders given Nicotine Patch + Bupropion (abstinence rate = 28.3%), should show an abstinence rate for responders + non-responders of 41.0%. Abstinence rates for Nicotine Patch Standard Treatment in several CSC trials using the similar recruitment and exclusion criteria range from 17-26%. With a conservative assumption that we will see the higher abstinence rates in our controls (e.g. 26%), our two Nicotine Patch-Based Treatment groups should show abstinence rates of **41.2% vs. 26%**. Sample size calculation using 2-tail test with continuity correction assuming  $p = 0.05$  and power = 80%, yields a minimum sample size of **298** in the nicotine patch arm. This study is designed with 150 in the Nicotine Patch arm and so it underpowered to reach this secondary outcome.

**Varenicline-Based Treatment (secondary outcome):** Power calculation for Varenicline Based Adaptive treatment vs. Varenicline Standard Treatment is based on abstinence rates observed in prior P50-funded trials as well as other published studies. To estimate the effect of adaptive treatment, a critical consideration is that 4 week Varenicline pre-cessation treatment without adaptation was superior to starting 1 week prior to quit day (Hajek et al 2011). Abstinence rate were 20.8% 1-week pre-quit start time. Hajek further showed that for participants starting 4 weeks prior to the Quit day, 35.4% of participants showed >50% reduction in cigs/day with an abstinence rate of 66.7% whereas 64.6% of participants failed to show >50% reduction in cigs/day and had an abstinence rate of 22.6%. The weighted average of these groups = 38.2%. Sample size calculation using **38.2% vs. 20.8%** with 2-tail test with continuity correction assuming  $p = 0.05$  and power = 80%, yields a minimum sample size of **208** within the Varenicline arm alone. This study is designed with 150 in the Varenicline arm and so it underpowered to reach this secondary outcome.

Version Date: 02/26/2020

**Full Sample (Primary Outcome):** Based on these calculations, a sample size of 300 for each of these comparisons should be sufficient to demonstrate significant differences between randomized arms (150 vs. 150). The Primary Outcome is a comparison of 12-week post-TQD smoking abstinence across the study sample (N=300). As stated above, the nicotine patch arm will require n=298 to reach significance, and the varenicline arm will require n=208 to reach significance. Neither arm (150 each) is powered to reach significance. The two arms together (n=300) are powered to reach primary outcomes. For the control group (nicotine patch arm = 26.0%; varenicline arm = 20.8%), an equally weighted sample would result in an abstinence rate of **23.4%**. For the adaptive treatment group (nicotine patch arm = 41.2%; varenicline arm = 38.2%), an equally weighted sample would result in abstinence rate of **39.7%**. A sample size calculation using 2-tail test with continuity correction assuming  $p = 0.05$  and power = 80% results in sample size of **248**. With 300 participants this study as power of 87% power for showing significant results on our primary outcome.

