#### **B. Efficacy of Adaptive Treatment:**

In this study, 50% of smokers will likely be classified as treatment responders. In a comparison across similar studies, treatment responders demonstrated 11-week post-quit 4-week continuous abstinence on nicotine patch at 39.0% and 36.9%, and 63.9% ( $p = 0.018$ ) on Varenicline (Rose & Behm, 2013, 2014; Rose et al., 2009). Varenicline alone was not significantly different from Varenicline + Bupropion at 70.0% ( $p = 0.99$ ) (Rose & Behm, 2014). In another P50 Study-4, pre-treatment Non-Responders demonstrated biochemically confirmed 11-week post-quit, 4-week continuous abstinence rate for: Varenicline + Bupropion = 44.4% vs. Varenicline alone = 18.6% ( $p = 0.001$ ,  $OR = 3.51$ , 95% CI = 1.64-7.51). This finding is supported by a recent Mayo Clinic study in which smokers achieved prolonged 12-week post-quit abstinence with Varenicline alone at 34.2% vs. Varenicline + Bupropion at 47.5%, ( $p = 0.04$ ,  $OR = 1.74$ , 95% CI = 1.04-2.93). If they are “treatment responders” they do not benefit significantly from the addition of Bupropion to Varenicline, but if they are non-responders, the addition of Bupropion appears to significantly improve abstinence rates, supporting the use of adaptive pharmacotherapy for Varenicline. Regarding use of the nicotine patch, we found that smokers did well using nicotine patch *if* they reduced their cpd by 50% during pre-quit treatment. Analysis of these “treatment responders” demonstrated biochemically-confirmed 4-week continuous abstinence at 11 weeks post-quit attempt of 54.2% in one study ( $n = 71$ ) and 59.0% in another study ( $n = 39$ ) (Rose & Behm, 2013, 2014). On the other hand, treatment non-responders showed 11-week post-quit attempt biochemically confirmed 4-week continuous abstinence at the following rates: Patch = 16.8% ( $n = 45$ ), vs. Patch + Bupropion = 39.5% ( $n = 38$ ) ( $p = 0.03$ ,  $OR = 3.0$ , 95% CI = 1.1-8.2), vs. Varenicline = 19.0% ( $n = 42$ ) ( $p = 0.88$ ,  $OR = 1.09$ , 95% CI = 0.37-3.2). This data suggests that it is reasonable to start smokers who choose the nicotine patch with just the patch, and then add Bupropion if they do not reduce cpd by 50% (Rose & Behm, 2014).

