### 3.6 Data Analysis and Statistical Considerations

**Detailed Data Analysis is provided in Section 13.** A summary of data analysis procedures includes the following: **Multilevel Modeling:** Given repeated observations across multiple individuals, many of the analyses in this study will be derived from multilevel modeling (MLM). **Missing Data:** Missing data will be examined to determine whether missingness is systematic (i.e., associated with individual baseline differences or time-related changes in observed variables). An intent-to-treat approach in which subjects lost to follow-up will be counted as non-abstinent will also be used to analyze univariate outcomes. An alpha criterion of 0.05 (two-tailed) will be used in all comparisons. **Analysis of Primary Outcome:** The primary study outcome is comparison of abstinence rates in adaptive vs standard treatment groups. The primary outcome measure is biochemically confirmed 30-day continuous abstinence at the 12-week post-quit attempt (carbon monoxide breath testing with CO < 7ppm). **Secondary abstinence outcomes:** Includes comparison of abstinence rates in adaptive vs standard treatment groups via self-reported 7 and 30-day continuous abstinence at 2- and 12-weeks post-TQD as well as phone-based self-reported abstinence at 1, 2, 6, 12, 26, and 52 weeks post-TQD. **Continuous Smoking Outcomes:** In addition to dichotomous outcomes described above, there will be an assessment of number of cpd and number of days abstinent at 2- and 12-week post TQD assessment visit (as well as phone assessment time points). **Assessment of potential moderators of primary effect:** The following constructs will be assessed as potential predictors of abstinence: demographics (age, gender, race, education), smoking history and heaviness, prior quit attempts, financial status, dependence (FTND), urge rating (MPSS), depression (PHQ-2), anxiety (GAD-2), alcohol use (AUDIT-C), stress (PSS-4), self-efficacy questions. **Assessment of potential mediators of primary effect:** The following constructs will be assessed to determine whether assignment to pharmacotherapy group is associated with change in these constructs pre- and post-treatment: urge rating (MPSS), depression (PHQ-2), anxiety (GAD-2), stress (PSS-4), self-efficacy. **Economic Analysis:** An economic analysis of the Algorithm vs. Standard treatment from multiple perspectives will be provided. **Sample Size Calculation:** Total sample size required to show differences on primary outcomes between pharmacotherapies and behavioral treatments with 10% downward adjustment in study group outcomes for possibility of unexpectedly poor outcomes is **N = 300**.

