**Analysis of Primary Outcome:** The primary outcome measure is biochemically confirmed 30-day continuous abstinence at the 12-week post-Target Quit Day (TQD) confirmed by carbon monoxide (CO) breath testing with CO < 7ppm. The study hypothesis is that adaptive treatment arms of the study will show higher smoking abstinence at 12-weeks post-quit attempt vs. non-adaptive treatment. An intent-to-treat approach will be taken to analyze primary outcomes such that all subjects who are enrolled in the study will be included in the primary analysis of outcomes. Outcomes will be analyzed using generalized linear regression modeling using an ANOVA-based design. An alpha criterion of 0.05 (two-tailed) will be used in all comparisons. For a conservative estimation of abstinence, subjects lost to follow-up after the point of randomization will be counted as non-abstinent. Following this, however, a sensitivity analysis will be conducted to determine the impact of this assumption, using multiple imputation procedures that model smoking outcomes in terms of “missingness” and smoking at previously observed time-points.

**Secondary smoking outcomes:** Analysis of secondary smoking outcomes will include comparison of abstinence rates in Adaptive vs. Non-Adaptive groups via self-reported 7 and 30-day continuous abstinence and number of cigarettes smoked per day at 2- and 12-weeks post TQD. Secondary smoking outcomes will be assessed using intent-to-treat principles with use of multiple imputation to account for missing data.

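### The Protocol's sample sizes and 87% power are labelled continuity-corrected but were computed without the correction, from a mis-carried patch rate; the synopsis's 10% downward adjustment is not in the calculation.

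*Protocol*

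**What the plan says.** In Section 13, under Sample Size Calculation, the patch and varenicline paragraphs give totals of 298 (41.2% vs 26%) and 208 (38.2% vs 20.8%) for 80% power. Both are described as two-tailed and continuity-corrected. The primary comparison pools the two strata with equal weight, 39.7% vs 23.4%, and uses the same description: "A sample size calculation using 2-tail test with continuity correction assuming" a p of 0.05 "and power = 80% results in sample size of 248". It then states: "With 300 participants this study as power of 87% power for showing significant results on our primary outcome".

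The patch paragraph derives its adaptive rate from responders and non-responders and says the group "should show an abstinence rate for responders + non-responders of 41.0"%. The full-sample paragraph uses a different figure: "For the adaptive treatment group (nicotine patch arm = 41.2%; varenicline arm = 38.2"%).

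Section 3.6 says N = 300 is the size needed to show differences between pharmacotherapies and behavioral treatments "with 10% downward adjustment in study group outcomes for possibility of unexpectedly poor outcomes".

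**The concern.** The 87% is the only power stated for the primary outcome. If the named method does not produce it, a reader cannot tell whether the method or the number is the intended one. At N = 248 the corrected test has 75.0% power, not the stated 80%.

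The 41.2% entered as an abstinence rate equals the proportion of patch responders quoted a few lines earlier in the same paragraph, so it looks like a transcription slip.

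The synopsis presents N = 300 as already allowing for results poorer than expected. Anyone relying on Section 3.6 alone would credit the design with a margin that the calculation does not show.

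**Working it through.** **Inputs** (Protocol, Section 13, Sample Size Calculation): two-sided alpha 0.05, 80% power, 1:1 allocation, 150 per arm. There is no inflation for dropout, because Section 10.6.3 says attrition is already within the abstinence rates.

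**Rates**
- Patch adaptive: 0.412 × 0.592 + 0.588 × 0.283 = 0.2439 + 0.1664 = 0.410.
- Varenicline adaptive: 0.354 × 0.667 + 0.646 × 0.226 = 0.2361 + 0.1460 = 0.382.
- Pooled control: (26.0 + 20.8)/2 = 23.4%.
- Pooled adaptive as stated: (41.2 + 38.2)/2 = 39.7%. With the derived patch rate: (41.0 + 38.2)/2 = 39.6%.

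**Reproducing 248.** Unpooled formula, no correction, per arm:
n = (1.960 + 0.842)² × [p1(1 − p1) + p2(1 − p2)] / (p1 − p2)²
= 7.849 × (0.2394 + 0.1792) / 0.163² = 123.67, so 124 per arm and **248** in total. This matches the stated figure.

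**Reproducing 87%.** At 150 per arm the standard error is √(0.4186/150) = 0.0528. Power = Φ(0.163/0.0528 − 1.960) = Φ(1.126) = **87.0%**. This also matches, again without correction.

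**Applying the correction.** n′ = (n/4) × [1 + √(1 + 4/(n·d))]², with d = 0.163:
- from the unpooled n of 123.67: 135.66, total 272;
- from the pooled-variance n of 126.41: 138.41, total 278.

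Power at 150 per arm, taking 1/150 off the difference and using the pooled null variance: Φ[(0.163 − 0.0067 − 1.960 × 0.0537)/0.0528] = Φ(0.968) = **83.4%**. Exact binomial enumeration of the corrected test gives 83.6%. The pooled formula without correction gives 86.3%.

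**All comparisons** (total N for 80% power; each range is unpooled to pooled variance):

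| Comparison | Stated | Uncorrected | Corrected |
|---|---|---|---|
| Primary, 39.7 vs 23.4 | 248 | 248–254 | 272–278 |
| Varenicline, 38.2 vs 20.8 | 208 | 208–214 | 232–236 |
| Patch, 41.2 vs 26 | 298 | 296–302 | 322–328 |
| Patch, 41.0 vs 26 | – | 304–310 | 330–336 |
| Primary, 39.6 vs 23.4 | – | 252–256 | 276–280 |

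Every corrected total is at least 24 above the stated one, which rounding cannot explain. With 39.6%, power at N = 300 is 85.9–86.6% uncorrected and 82.9% corrected (pooled variance).

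**The 10% adjustment.** The pooled 39.7% is the plain mean of 41.2% and 38.2%, so no reduction was applied. Section 3.6 does not say what is reduced. Power at N = 300 under the possible relative readings:

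| Reading | Rates | Corrected | Uncorrected |
|---|---|---|---|
| Adaptive rate × 0.9 | 35.7 vs 23.4 | 60% | 65–66% |
| Difference × 0.9 | 38.1 vs 23.4 | 75% | 79–80% |
| Both arms × 0.9 | 35.7 vs 21.1 | 77% | 81% |

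These start from 39.7%; starting from 39.6% lowers each by less than one point. Section 7.2 contrasts study group with control group, which makes the first row the natural reading. On that row, 80% power would need 424–428 uncorrected, or 460 corrected (pooled variance).

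**The case against.** The best defence is that the label is wrong, not the numbers. The planned primary analysis is generalized linear regression with an ANOVA-based design, and no continuity-corrected test is planned anywhere. For that analysis about 87% is a fair figure. This stands, and it is why deleting the label is a legitimate repair.

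It is also true that nothing about the design turns on this. N = 300 exceeds every version of the primary total, and the Protocol already says each stratum alone is underpowered. A reader might infer that the trial itself is underpowered; the Protocol's figures do not support that.

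A reader might also infer that the synopsis claim is false on any reading, with power of 60–66%. That range belongs only to a 10% relative fall in the adaptive rate alone. If both arms fall by 10%, uncorrected power is about 81%. What can be said is that Section 13 does not contain the adjustment.

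Nor can one say there is no conservatism at all. The patch control rate is set at the top of a 17–26% range, and the varenicline adaptive rate assumes no bupropion benefit in non-responders (22.6%, against 44.4% quoted for the combination in Section 3.2). These are real cushions, but they are not the 10% adjustment that Section 3.6 describes.

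Finally, one could substitute the lower patch figures in Section 3.2 ("treatment responders demonstrated 11-week post-quit 4-week continuous abstinence on nicotine patch at 39.0% and 36.9"%) for the 59.2% used and obtain much lower power. The same section also quotes 54.2% and 59.0% for patch responders, and the Protocol gives no ground for choosing only the two lowest.

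**Conclusion.** The stated figures do not follow from the stated method. The totals 248 and 208 and the 87% power are uncorrected unpooled results, and 298 is within 2 of one. The named correction raises the primary total by 24 to 30 and lowers power at N = 300 from about 87% to about 83%.

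The 41.2% is a carry-forward error. It moves the pooled rate by 0.1 point and power by about 0.4 point: small, but plainly inconsistent within one paragraph.

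The synopsis adjustment is unsupported by the calculation. It fails on the natural reading, and with the continuity correction it leaves power below 80% on all three readings in the table. Without the correction, it holds if both arms fall by 10%.

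All of this rests on the Protocol's own rates, 1:1 allocation and normal-approximation formulas. It is a reporting error in the power justification, not a shortfall in sample size.

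**What to change.** In Sample Size Calculation, replace the patch adaptive rate of 41.2% by 41.0% and the pooled 39.7% by 39.6%. Leave the responder share of 41.2% where it is used as a share. Then choose one method, name the variance formula, and use it throughout:

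- **(a)** delete the continuity-correction label and restate patch 304–310, varenicline 208–214, total 252–256, and power of about 86–87% at N = 300; or
- **(b)** keep the correction and restate patch 330–336, varenicline 232–236, total 276–280, and power of about 83%.

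Option (a) fits the planned regression analysis more closely. The lower end of each range of totals is the unpooled formula and the upper end the pooled one.

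In Section 3.6, delete the 10% adjustment and the reference to behavioral treatments. Alternatively, define what is reduced and state the resulting power at N = 300: about 60–66% for the adaptive rate alone, 75–80% for the difference, or 77–81% for both arms. Remove the matching reference to behavioral groups under Statistical Hypothesis, Model, and Method of Analysis, since Section 3.2 gives every participant the same single visit.

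The cost is wording in an amendment, with the stated power unchanged or slightly less favourable. N stays at 300 and no patients are added.

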## **14 ADMINISTRATIVE AND ETHICAL CONSIDERATIONS**

### **14.1 Regulatory and Ethical Compliance**

This protocol was designed and will be conducted and reported in accordance with the International Conference on Harmonization (ICH) Harmonized Tripartite Guidelines for Good Clinical Practice, the Declaration of Helsinki, and applicable federal, state, and local regulations.

### **14.2 DUHS Institutional Review Board and DCI Cancer Protocol Committee**

The protocol, informed consent form, advertising material, and additional protocol-related documents must be submitted to the DUHS Institutional Review Board (IRB) and DCI Cancer Protocol Committee (CPC) for review. The study may be initiated only after the Principal Investigator has received written and dated approval from the CPC and IRB.

The Principal Investigator must submit and obtain approval from the IRB for all subsequent protocol amendments and changes to the informed consent form. The CPC should be informed about any protocol amendments that potentially affect research design or data analysis (i.e. amendments affecting subject population, inclusion/exclusion criteria, agent administration, statistical analysis, etc.).

The Principal Investigator must obtain protocol re-approval from the IRB within 1 year of the most recent IRB approval. The Principal Investigator must also obtain protocol re-approval from the CPC within 1 year of the most recent IRB approval, for as long as the protocol remains open to subject enrollment.

### **14.3 Informed Consent**

The informed consent form must be written in a manner that is understandable to the subject population. Prior to its use, the informed consent form must be approved by the IRB.

The Principal Investigator or authorized key personnel will discuss with the potential subject the purpose of the research, methods, potential risks and benefits, subject concerns, and other study-related matters. This discussion will occur in a location that ensures subject privacy and in a manner that minimizes the possibility of coercion. Appropriate accommodations will be made available for potential subjects who cannot read or understand English or are visually impaired. Potential subjects will have the opportunity to contact the Principal investigator or authorized key personnel with questions, and will be given as much time as needed to make an informed decision about participation in the study.

Before conducting any study-specific procedures, the Principal Investigator must obtain written informed consent from the subject or a legally acceptable representative. The original informed consent form will be stored with the subject's study records, and a copy of the informed consent form will be provided to the subject. The Principal Investigator is responsible for asking the subject whether the subject wishes to notify his/her primary care physician about participation in the study. If the subject agrees to such notification, the Principal Investigator will inform the subject's primary care physician about the subject's participation in the clinical study.

### **14.4 Study Documentation**

Study documentation includes but is not limited to source documents, case report forms (CRFs), monitoring logs, appointment schedules, study team correspondence with sponsors or regulatory bodies/committees, and regulatory documents that can be found in the DCI-mandated "Regulatory Binder", which includes but is not limited to signed

protocol and amendments, approved and signed informed consent forms, FDA Form 1572, CAP and CLIA laboratory certifications, and clinical supplies receipts and distribution records.

Source documents are original records that contain source data, which is all information in original records of clinical findings, observations, or other activities in a clinical trial necessary for the reconstruction and evaluation of the trial. Source documents include but are not limited to hospital records, clinical and office charts, laboratory notes, memoranda, evaluation checklists, pharmacy dispensing records, recorded data from automated instruments, copies or transcriptions certified after verification as being accurate copies, microfiches, photographic negatives, microfilm or magnetic media, x-rays, subject files, and records kept at the pharmacy, at the laboratories and at medico-technical departments involved in the clinical trial. When possible, the original record should be retained as the source document. However, a photocopy is acceptable provided that it is a clear, legible, and an exact duplication of the original document. An electronic case report form (CRF) will be the primary data collection document for the study. The CRFs will be updated within two weeks of acquisition of new source data. Only approved study staff (please specify names and/or titles of authorized individuals as stated in key personnel), are permitted to make entries, changes, or corrections in the CRF. For paper CRFs, errors will be crossed out with a single line, and this line will not obscure the original entry. Changes or corrections will be dated, initialed, and explained (if necessary). The Principal Investigator or authorized key personnel will maintain a record of the changes and corrections. For electronic CRFs, an audit trail will be maintained by the electronic CRF management systems, REDCap and Epic Dashboard.

